## Abstract

**Methods::**

This study is a prospective, multicenter, assessor-blind, 3-arm, parallel-group, randomized, waitlist-controlled trial. In total, 90 patients will be randomly assigned to the electroacupuncture, electroacupuncture and warm needing, or waitlist control group in a 1:1:1 ratio. Patients in the 2 treatment groups will be treated twice a week for a total of 5 weeks. Patients in the control group will not receive treatment during the study period and will be informed that they can receive it for free after a 10-week waiting period. The duration of intervention for this study will be 5 weeks, followed by another 5 weeks for the posttreatment assessment. The primary outcome is the change in the visual analog scale score for tinnitus loudness from baseline until the end of treatment. The secondary outcome is the tinnitus discomfort assessment measured using the Tinnitus Handicap Inventory. Outcome parameters will be assessed at baseline and at weeks 5 and 10. Any adverse events will be observed and recorded for safety assessment. Linear mixed models for repeated measures will be applied in the analysis.

**Discussion::**

Acupuncture and moxibustion could be potentially effective treatment alternatives for tinnitus. The study results will provide evidence to determine the efficacy and safety of electroacupuncture with or without warm needling for tinnitus.

## 1. Introduction

Tinnitus is a common auditory condition in otolaryngology practice. It refers to the perception of sound in the ear or brain, in the absence of external auditory stimulation.^[1–3]^ People usually experience an auditory phantom sensation even when no external sound is present. It can be any sound but is typically characterized as a ringing, hissing, buzzing, whistling, or roaring sound heard in 1 or both ears, or somewhere inside the head.^[1]^

Epidemiological studies report a wide range prevalence of tinnitus in adults ranging from 5.1% to 42.7%.^[4]^ In China, the prevalence of tinnitus ranges from 4.3% to 51.3%; however, it varied with age and sex.^[5]^

The pathophysiological mechanism of tinnitus is complex and not well-defined.^[6]^ While many people with tinnitus are able to manage it, it can also become a significant issue and may have a major impact on daily life, potentially leading to suicidal thoughts and attempts.

Previous studies indicated that the prevalence of tinnitus increases with age.^[5–7]^ Among older adults, 1 study showed that 1 in 5 persons has tinnitus and every 1 out of 10 with tinnitus experienced severe tinnitus that interferes with daily life, and those with hearing impairment were twice as likely to have tinnitus compared to those without.^[8]^ Additionally, the prevalence and risk of developing tinnitus are associated with sex, hearing loss, otological comorbidity, systemic diseases, sleep disorders, stress, depression, and smoking.^[5–7]^

Various treatment approaches are currently used in clinical settings with varying levels of evidence, including cognitive behavioral therapy, tinnitus retraining therapy, counseling, hearing aids, cochlear implant therapy, and drug therapy.^[1,2,6]^ However, the best way to manage tinnitus remains inconclusive, and the methodological quality of studies varies. In addition, no specific therapy has been proven to be effective in completely eliminating tinnitus.

Acupuncture, one of the treatment modalities in traditional Chinese medicine (TCM) for tinnitus,^[9]^ has been widely used and recommended for tinnitus relief in China for a long time.^[10]^ The use of acupuncture for tinnitus was initially discussed in the Huangdi Neijing. Acupuncture and moxibustion can help relieve tinnitus by regulating the flow of blood and *qi*.^[10]^ Previous systematic reviews have shown promising results for manual acupuncture, electroacupuncture, or warm needling in reducing the loudness and disability of tinnitus.^[11–13]^ A Bayesian analysis showed that there was a trend of greater effectiveness of warm needling in the treatment of neurological tinnitus,^[14]^ but with limitations in study methodology and evidence.

To date, there is a lack of rigorous evidence for effective therapies to reduce or eliminate tinnitus. Further research on the therapeutic effects of acupuncture for tinnitus is warranted, and should be conducted according to higher methodological standards. Finally, given the importance of the health problem of tinnitus, a well-designed randomized controlled clinical trial is proposed.

Therefore, this study aims to explore and determine the efficacy and safety of electroacupuncture (EA) and electroacupuncture combined with warm needling (EAWN) for the treatment of subjective tinnitus among older adults in Hong Kong, and report the short-term follow-up results. We will compare the effects of the 2 acupuncture treatment groups and the control group in reducing the loudness of tinnitus and improving the impairment caused by tinnitus.

## 2. Methods

### 2.1. Study design and setting

This study is a prospective, multicenter, assessor-blind, triple-arm, parallel-group, randomized controlled trial with a 1:1:1 ratio of group allocation to EA, EAWN, or waitlist control (control group, who can receive acupuncture treatment after a 10-week waiting period). Ninety eligible participants will be recruited for this study. The entire study period will last for 10 weeks, including a 5-week intervention period and a 5-week follow-up period. Outcome assessments will be performed at baseline and at weeks 5 and 10 through telephone or face-to-face evaluations. The study will be conducted at 3 Chinese medicine clinics under the management of Pok Oi Hospital, namely, Pok Oi Hospital − The Chinese University of Hong Kong Chinese Medicine Clinic cum Training and Research Centre (Shatin District), Pok Oi Hospital − The Chinese University of Hong Kong Chinese Medicine Clinic cum Training and Research Centre (Yuen Long District), and Pok Oi Hospital − Chinese Medicine Polyclinic (Tin Shui Wai). The study protocol is written following the Standard Protocol Items: Recommendations for Interventional Trials 2013 Statement and the Standard Protocol Items for Clinical Trials with TCM 2018 checklists.^[15,16]^

### 2.2. Study population

This study will focus on subjects aged between 50 and 70 years with tinnitus for half a month to 24-month duration. Eligibility criteria have been developed mainly to enroll appropriate subjects and exclude those with serious diseases or contraindications to treatment.

#### 2.2.1. Inclusion criteria

Participants diagnosed with subjective tinnitus^[1]^ and able to communicate normally in Chinese will be recruited in the study if they satisfied all of the following criteria: Males and females aged 50 to 70 years; Unilateral or bilateral tinnitus for 0.5 to 24 months; Loudness of tinnitus rated ≥ 3 points on a 0 to 10 numeric rating scale (NRS) at the time of enrollment; Agree to sign the informed consent form voluntarily.

#### 2.2.2. Exclusion criteria

Subjects will be excluded if they possess any of the following criteria: Known disease conditions that could cause tinnitus, including Meniere syndrome, external auditory canal diseases, and middle ear diseases; History of head trauma; Currently using a cardiac pacemaker or metal implants; Known severe cardiac diseases, cerebrovascular diseases, renal diseases, or hematologic diseases; Known severe psychiatric or psychological disorder; Pregnant, lactating, or expecting a pregnancy during the study period; Severe needle phobia; Known hypersensitive reaction following acupuncture and moxibustion treatment or an inability to cooperate with the acupuncture and moxibustion procedure; Incapable to understand and answer the questions of the assessors in the study; Other factors deemed unsuitable for inclusion in the study by investigators.

### 2.3. Recruitment procedure and study flow

Subjects will be recruited from all Chinese medicine centers, polyclinics, and mobile clinics under the management of Pok Oi Hospital. These sites cover all districts in Hong Kong. Subjects interested in participating in the study will be referred to or self-approached by the 3 dedicated Chinese medicine centers to undergo eligibility assessment. They will be prescreened through telephone interviews. Potential participants will undergo a face-to-face interview to confirm their eligibility for the study. During the interview, the investigators will explain the overall objectives and nature of the study, and undergo the eligibility assessment and informed consent process. A 4-week washout period will be required for those receiving acupuncture therapies before enrollment. If the subject consents, sociodemographic and clinical data, including sex, age, and medical history will be collected. Additionally, baseline assessments of primary and secondary outcome measures will be conducted. They will then be randomly assigned to 1 of the 3 groups by an independent staff member who is not involved in the study. A schedule for treatment and follow-up procedure will be assigned. After enrollment, the study site will strive to keep track of the participants throughout the study to maintain participation and complete follow-up assessments. The study flow is shown in Figure 1 and Figure 2 demonstrates the schedule of enrollment, interventions, and assessments.

**Figure 1. F1:**
[figure not shown]
The study flowchart.

**Figure 2. F2:**
[figure not shown]
Schedule of enrollment, interventions, and assessments. ^1^ Visits for ± 4 days are allowed for week 10 follow-up assessments. EA = electroacupuncture, EAWN = electroacupuncture and warm needling.

### 2.4. Randomization and blinding

The treatment allocation of EA, EAWN, or waitlist control for each eligible subject in the study will be determined through a randomization process. Participants will be told that they will be randomized to 1 of 3 groups: EA for 5 weeks followed by observation for 5 weeks; EAWN for 5 weeks followed by observation for 5 weeks; or observation for 10 weeks followed by EA or EAWN for 5 weeks. Treatment or assessment will be scheduled to avoid contact between the participants. The random allocation to the 3 arms of the study will be generated using Random Allocation Software,^[17]^ following a balanced 1:1:1 ratio. A standard block size of 6 will be used, which will not be revealed to the site investigators. This will be performed by an independent administrator who is not involved in the study, and the information on the random allocation list will remain strictly confidential. The randomization result will be kept in sequentially numbered, opaque, sealed envelopes to ensure allocation concealment. In this study, practitioners and patients will not be blinded; however, the outcome assessors will be blinded to the intervention assignment.

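### The single block size of 6 is meant to be withheld from site investigators but is printed in the public article; with practitioners and patients unblinded, up to one allocation in five could be deduced

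*Protocol article*

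**What the plan says.** Section 2.4 of the protocol article generates the list "following a balanced 1:1:1 ratio" and adds: "A standard block size of 6 will be used, which will not be revealed to the site investigators". No other block size is named. The same section states that "practitioners and patients will not be blinded; however, the outcome assessors will be blinded to the intervention assignment".

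The concealment measures are these:
- An outside person prepares the list, which is to stay confidential: "This will be performed by an independent administrator who is not involved in the study" (section 2.4).
- "The randomization result will be kept in sequentially numbered, opaque, sealed envelopes to ensure allocation concealment" (section 2.4).
- Assignment follows eligibility, consent and baseline assessment: "They will then be randomly assigned to 1 of the 3 groups by an independent staff member who is not involved in the study" (section 2.3).

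The trial runs at three clinics (section 2.1). The article does not say whether they share one list or have one each. The last exclusion criterion is open-ended: "Other factors deemed unsuitable for inclusion in the study by investigators" (section 2.2.2).

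**The concern.** The plan treats the block size as something site investigators should not know, then puts it where they can read it. Once the size is known, a constant block lets past allocations reveal future ones. Because treatment is not masked from practitioners or patients, past allocations can become known at the clinics. Sequentially numbered envelopes may also show the position within a block, if numbering starts at 1 and follows the list.

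What is at stake is who gets enrolled, and when. The waitlist arm means ten weeks without treatment (section 2.6.3), so an enroller who expects that allocation has a conceivable reason to defer or exclude a patient, and the discretionary exclusion gives room to do so. The primary outcome is a self-rated 0 to 10 loudness score (section 2.9.1). The model adjusts for age and tinnitus duration only (section 2.13.2). Selection on expectation or unmeasured prognosis would survive both that adjustment and the intention-to-treat analysis, because it acts before randomization.

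**Working it through.** **Inputs.** Block size 6, three arms at 1:1:1, hence 2 + 2 + 2 per block (section 2.4); 90 patients (section 2.13.1); three clinics (section 2.1). The plan gives no predictability figure to reproduce. Its numbers fit together: 90 / 6 = 15 blocks, and 15 × 2 = 30 per arm.

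**Upper bound: the observer knows the block size and where blocks start, and sees every earlier allocation.**

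A block has 6! / (2! 2! 2!) = 90 equally likely orderings.

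*Certain allocations.* Slot 6 is always known. Slot 5 is known when the last two slots belong to the same arm: 3 / C(6,2) = 3/15 = 1/5. Slots 1 to 4 are never certain. Share = (1 + 0.2) / 6 = 20%, and 0.20 × 90 = 18 allocations.

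*Waitlist known to be used up.* By slot i the probability is C(i−1,2) / 15, which gives 1/15, 3/15, 6/15 and 10/15 for slots 3 to 6. Share = (20/15) / 6 = 22.2%.

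*At least one arm ruled out.* Probabilities for slots 3 to 6 are 0.2, 0.6, 1 and 1. Share = 2.8 / 6 = 46.7%, including the certain allocations.

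*Best guess.* The hit rates by slot are 1/3, 0.4, 0.5, 0.533, 0.6 and 1. They sum to 3.367, and 3.367 / 6 = 56.1%, against 33.3% by chance.

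**Lower figure: one list shared by three equal clinics, with the observer seeing only their own.**

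This is an assumption, since the article states neither the list structure nor site shares. Each earlier allocation is then seen with probability 1/3. Certainty in slot 5 or 6 requires having seen all four allocations that exhaust the other two arms, so each term is multiplied by (1/3)⁴ = 1/81.

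Share = (1.2 / 6) × (1/81) = 0.25%, about 0.2 of 90. Knowing that the waitlist arm is used up needs two sightings: 22.2% × (1/3)² ≈ 2.5%.

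**Varying block sizes.** These are simulated lists of 90, with sizes drawn with equal probability. The observer sees every earlier allocation and knows the set of sizes but not the current one.

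| Block sizes | Known with certainty | Best guess correct |
|---|---|---|
| 6 only | 20% | 56% |
| 3 or 6 | 8.6% | 58% |
| 6 or 9 | 5.1% | 54% |
| 3, 6 or 9 | 3.8% | 55% |
| 6, 9 or 12 | 2.4% | 53% |

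Varying the size removes most certain allocations. It does little to best-guess accuracy, and the 3-or-6 scheme makes that slightly worse.

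**The case against.** A fixed block with independent, concealed allocation is a legitimate design, and varying the size improves it rather than corrects an error. A reader might infer from the arithmetic that one allocation in five in this trial is predictable. The article does not support that. Deduction at that rate needs one enrolling person who knows the size, the block boundaries and every earlier allocation. Investigators handle eligibility and consent, and nothing says that they follow the sequence. Waitlist patients receive no intervention and may be followed by telephone (section 2.1), so a treating practitioner need not learn of those allocations. With a shared list and site-only knowledge, the figure is close to zero.

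A reader might also infer that enrolment was or will be steered. Nothing shows this. The discretionary exclusion is a general judgement clause. Assignment comes after consent and baseline, so steering would have to happen earlier, on a prediction. The article also does not show that recruitment was open when it appeared. Finally, calling the trial open-label without qualification would be wrong, because outcome assessors are blinded.

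All of this stands, and it limits the size of the point. It does not remove it. The envelopes, the confidential list and the independent assigner stop someone from seeing the next allocation, not from working it out. Assessor blinding acts only after enrolment. The disclosure of a figure that the plan says is withheld is plain in the text.

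**Conclusion.** The point holds as a weakness in concealment with a wide range. With the fixed block known, between about 0.25% and 20% of allocations could be deduced with certainty. The upper end assumes an enroller who sees every earlier allocation on the list, as could happen with separate site lists or full sharing between clinics. The lower end assumes one list, three equal clinics and no sharing. The article does not say which applies. Selective enrolment is possible, not shown, and no bias in the loudness score can be put to it from the document. The change is a cheap improvement worth making while envelopes remain unused.

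**What to change.** 1. The independent administrator regenerates the unused remainder of the list with block sizes that vary at random in multiples of 3, for example 6 and 9, or 6, 9 and 12. Mixing only 3 and 6 gains less.
2. The sizes and their range stay undisclosed until recruitment closes. Deleting the 6 from the protocol would not be enough, because the published figure cannot be withdrawn.
3. The protocol states whether there is one list or one per clinic.
4. If recruitment has already closed, the trial report names the disclosed fixed block as a limitation and says how the lists were organized.

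The cost is a short piece of work for the administrator, a new set of envelopes and a brief protocol change. Section 2.16 requires ethics-committee approval of an amendment before any change takes effect. Arm sizes may differ by a few patients if the last block is incomplete. The gain is the removal of most certain allocations; best-guess accuracy would drop only from 56% to about 53% to 55% with 6/9/12 or 3/6/9.

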### 2.5. Qualifications of practitioners

The treatments of the study will be conducted by Hong Kong registered Chinese medicine practitioners who have over 3 years of experience in acupuncture and are trained in administering EAWN treatment. The registered Chinese medicine practitioners in this study will strictly adhere to the study protocol and be trained in administering study treatments.

### 2.6. Treatment procedure

The style of acupuncture and moxibustion used in this study is based on TCM theory. Furthermore, the selection of acupuncture points and treatment regimens will be based on a review of the literature and previous studies,^[13,18]^ and expert opinion. The treatments will be provided free of cost to all the subjects.

#### 2.6.1. EAWN group

EAWN therapy will be performed twice per week for 5 weeks, for a total of 10 treatment sessions. During each treatment session, standardized procedures will be performed. For subjects with tinnitus on both sides, treatment will be provided bilaterally. The acupuncture points used will be Tinggong (SI19) and Yifeng (TE17) on the affected side; Baihui (GV20) and Yintang (GV24^+^); bilateral posterior temporal line (the scalp acupuncture line MS11); Zhongzhu (TE3) and Zusanli (ST36) on the affected side.^[19–21]^ Treatments will be administered using sterile, single-use, disposable acupuncture needles (0.25 mm × 25/40 mm; ARight Brand, Suzhou Medical Appliance Factory, Suzhou, China). Room temperature will be maintained at 25 ± 3^o^C during treatment. The subjects will lie down in a supine position during the treatment sessions. First, the skin will be sterilized before needle insertion. Subsequently, needles will be inserted in the following sequence: perpendicularly for SI19 (depth, 20 mm) and TE17 (depth, 20 mm); transversely for GV20 (depth, 15 mm), GV24^+^ (depth, 10 mm), and from Shuaigu (GB8) to Qubin (GB7) along MS11 (depth, 20 mm); perpendicularly for TE3 (depth, 10 mm) and ST36 (depth, 25 mm). Next, stimulation will be performed by twirling the needles evenly to achieve a dull ache, numbness, or heaviness sensation, referred to as deqi.^[22,23]^ After obtaining deqi, the tonifying method will be applied to ST36, and the neutral supplementation method will be applied to the remaining acupuncture points. All needles will be retained in situ for 25 minutes. During the retention period, electrical stimulation and warm needling will be performed simultaneously. Paired electrodes of the electroacupuncture apparatus (Hwato SDZ-III, Suzhou Medical Appliance Factory, Suzhou, China) will be connected to the needles at the ipsilateral SI19 and TE17, GV20 and GV24^+^, and bilateral MS11. Electrical stimulation will be delivered using dense-disperse waves at a frequency of 2 Hz. The intensity of the electric current will be increased to the patient’s maximum tolerance and then slightly reduced to a bearable and comfortable level (<10 mA). For warm needling, the bottom of a cylinder-shaped moxa stick (Changsha Furong Huai, Changsha, China) made of mugwort, measuring 11 mm in diameter and 15 mm in length, and weighting 0.7 ± 0.05 g will be ignited and attached to the needle handle (the needle handle is inserted into the center of the cylinder-shaped moxa stick) of SI19 and TE17. The ignited end of the moxa stick is positioned 35 mm from the skin surface, which is a safe and appropriate distance for the administration of moxibustion.^[24–27]^ After the first moxa stick burns out, the ashes will be removed, and the second stick will be placed following the same procedure. In total, 2 moxa sticks will be applied individually to each acupuncture point of SI19 and TE17. The burning time for each moxa stick is approximately 10 minutes. The total moxibustion time for 2 moxa sticks will be approximately 20 minutes, which is an advisable time for effective thermal stimulation of moxibustion.^[24,28]^ During warm needling therapy, the subject will feel a sense of local warmth, and the surrounding skin may become mildly red without any burning pain. The needles will be removed after the retention time and at the end of the moxibustion procedure.

During warm needling, precautionary measures should be taken. To prevent skin burns, the practitioner should hold the junction of the needle body with one hand and gently inserts the ignited moxa stick into the needle at the inserted acupuncture points with the other hand. After attaching the moxa stick to the needle handle, the practitioner should ensure that the stick is fully fixed to the needle handle to prevent it from falling onto the skin surface. When replacing the second moxa stick and removing the needles at the end of the treatment, the practitioner should carefully to check the temperature of the needles to prevent burns. The practitioner must be aware of the subject’s sensitivity to temperature and pain, and advise the subject not to let the acupuncture points become uncomfortably hot. The subject will be closely monitored during the entire procedure to ensure safety, and that any accident will be handled in a timely manner.^[29]^

